### 2.3. Heart Rate Variability

Data collection of the electrocardiogram (ECG) will be conducted using the Neuro-EMG Micro equipment and PolySpectrum software (Neurosoft, Russia, version 5.3.1.0 released 15 November 2017, with a sampling frequency of 1000 Hz and a 60 Hz notch filter. The patient will remain seated and motionless in a comfortable chair to allow for acclimatization and autonomic stabilization. During this period, the electrodes (RA, LA, LL) will be placed, and signal quality will be continuously monitored. After stabilization, a 5 min baseline will be collected. Subsequently, an additional 7 min of data will be recorded for heart rate variability (HRV) analysis.

The analysis will be performed using Kubios HRV Scientific software (ver. 4.1, Win & Mac, October 2023), calculating measures in the time domain (SDNN, RMSSD, and pNN50), in the frequency domain (VLF, LF, HF, and LF/HF ratio), and sample entropy (SampEn). The factory default settings will be used, including automatic artifact correction at a medium level, automatic beat correction, an interpolation rate of 4 Hz, and a trend removal method. All collections and analyses will adhere to the guidelines set forth by the Task Force of the European Society of Cardiology and the North American Society of Pacing and Electrophysiology (1996).

### 2.4. Neuropsychological Assessment

The Brazilian version of the Measurement and Treatment Research to Improve Cognition in Schizophrenia Consensus Cognitive Battery (MATRICS) is a standardized cognitive assessment for patients with schizophrenia and it will be used to assess changes in cognition. In this study, 9 of 10 subtests from the MATRICS were chosen, given the low-reliability coefficient of MSCEIT in the Brazilian version [39]. We will analyze the following domains: Speed of processing: Trail Making Test: Part A (TMTA); Brief Assessment of Cognition in Schizophrenia (BACS): Symbol Coding and Category Fluency Test: Animal naming (Fluency); Attention: Continuous Performance Test—Identical Pairs (CPT-IP); Working memory: Wechsler Memory Scale—Third Edition (WMS-III): Spatial Span (SS) and Letter-Number Span Test (LNS); Verbal learning: Hopkins Verbal Learning Test—Revised (HVLT-R); Visual learning: Brief Visuospatial Memory Test—Revised (BVMT-R); Reasoning and problems solving: Neuropsychological Assessment Battery (NAB): Mazes. The intelligence coefficient (IQ) will be estimated by the composite score of the subtests of Vocabulary and Matrix Reasoning from the Brazilian Version of the Wechsler Adult Intelligence Scale—3rd edition [47].

### 2.5. Statistical Analysis

The effects of the intervention will be analyzed according to the intention-to-treat (ITT) paradigm, which assesses the effect on all participants, regardless of their level of adherence to the treatment. The primary outcome of the study will be the reduction of negative symptoms, measured by the total score of the Brief Negative Symptom Scale (BNSS) with a score ≥20, while the secondary outcomes will focus on the reduction of negative symptoms as assessed by the negative symptom subscale score of the Positive and Negative Syndrome Scale (PANSS), the sub-domains of BNSS and physiological variables, through HRV assessment, sleep alterations and their association with negative symptoms, assessed by Pittsburgh and Epworth scales, and cognitive assessment by the MATRICS.

Missing data during follow-up will be handled using the restricted maximum likelihood method in mixed-effects linear regression analyses, allowing for the use of all data regardless of whether a participant completes the study, consistent with ITT analysis.

Clinical and demographic differences between groups will be initially evaluated at baseline using the Chi-square test for categorical variables and Student’s *t*-test for independent samples in continuous variables. These same tests will also be employed to identify potential differences between participants who complete the study and those considered to be dropouts. A participant will be considered a dropout if they miss any of the intervention protocol sessions, resulting in a loss of four sessions of intermittent theta burst stimulation (iTBS). A significance level of *p* < 0.05 will be adopted in all statistical analyses.

Differences between the baseline, after intervention, and follow-up (T0, T1, and T2) for each measure will be tested using mixed-effects linear models. The treatment effect will be estimated through the interaction between the intervention group (intervention or sham) and the assessment time (T0, T1, and T2). Effect estimates will be presented as post-intervention mean differences, along with 95% confidence intervals, *p*-values, and Cohen’s d effect sizes (where 0.2 represents a small effect, 0.5 represents a moderate effect, and 0.8 represents a large effect). Random effects from repeated measures within each subject will be modeled according to the covariance structure that shows the lowest index based on the Akaike information criterion (AIC). The following covariates will be included in the models: the Calgary Depression Severity Scale score, as depressive symptoms may confound the assessment of negative symptoms and individuals with severe depression will be excluded from the sample; the total score of the Clinical Global Impression-Severity scale (CGI-S), since the severity of illness may influence treatment response; and the Generalized Anxiety Disorder 7-item scale (GAD-7), due to anxiety symptoms. For the various exploratory analyses conducted with the previously detailed secondary outcomes, the significance value will be corrected for multiple tests using Bonferroni criterion, with an alpha of 0.05 divided by the number of tests.

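### Section 2.5 gives two significance rules that overlap on the secondary outcomes, p < 0.05 everywhere and Bonferroni, without saying which governs their group-by-time tests (minor; primary result unaffected)

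*Protocol article*

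**What the plan says.** All of this is in the protocol article.

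- **General rule (2.5. Statistical Analysis).** After naming the primary and secondary outcomes, and at the end of the paragraph on baseline and dropout comparisons, the article states that p < 0.05 "will be adopted in all statistical analyses". No exception is attached.
- **Rule for the secondary outcomes (2.5, following paragraph).** "For the various exploratory analyses conducted with the previously detailed secondary outcomes, the significance value will be corrected for multiple tests using Bonferroni criterion". Each such test is thus judged at 0.05/m, where the count m is not given.
- **Secondary outcomes (2.5).** The first is the "negative symptom subscale score of the Positive and Negative Syndrome Scale (PANSS"). Next come "the sub-domains of BNSS and physiological variables, through HRV assessment". The rest are sleep on the Pittsburgh and Epworth scales together with its association with negative symptoms, and MATRICS cognition.
- **Components.** For heart rate variability (2.3), the software is used for "calculating measures in the time domain (SDNN, RMSSD, and pNN50), in the frequency domain (VLF, LF, HF, and LF/HF ratio), and sample entropy (SampEn"), which is eight measures. For cognition (2.4), "9 of 10 subtests from the MATRICS were chosen", and the section then lists six domains for analysis.

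**The concern.** The two statements overlap on the secondary outcomes, and no sentence ranks them. There are two separate gaps.

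1. The first rule covers every analysis, and the second covers a subset of the same analyses at a stricter level. The article does not say that the second overrides the first.
2. The second rule is limited to exploratory analyses conducted with the secondary outcomes. The article does not call the secondary outcomes themselves exploratory, and its list mixes treatment effects with associations (sleep and negative symptoms). The Bonferroni sentence could therefore cover the group-by-time tests, or only further analyses such as the associations. In the second case the group-by-time tests fall back to 0.05.

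At stake is whether a given result for PANSS negative, a BNSS sub-domain, HRV, sleep or cognition may be reported as significant. The Introduction's hypothesis includes improvement in sleep patterns, symptom severity and cognition, so some of these results will carry claims.

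**Working it through.** **Inputs**

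- 30 per group, f = 0.38, 5% two-tailed, stated power 0.82 (section 2, Participants).
- Count of tests m from the article: PANSS negative 1 + HRV 8 + sleep scales 2 + MATRICS domains 6 = 17. BNSS sub-domains are left out because the article does not give their number.
- Assumption where sub-domains are counted: 5, giving m = 17 + 5 = 22.

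**Step 1: the plan's own figure.** For two groups d = 2f = 2 × 0.38 = 0.76. With 30 per arm the noncentrality is d × √(30/2) = 0.76 × √15 = 2.943. On 58 degrees of freedom the two-sided 5% critical value is t = 2.002. Noncentral t gives power 0.825, which agrees with the stated 0.82. The primary analysis and its 5% level are consistent.

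**Step 2: the threshold under each rule.** The smallest observed standardised difference that reaches significance is d_min = t_crit / √15. This treats each test as a two-group comparison on 58 degrees of freedom.

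| Rule | Per-test alpha | t_crit | d_min |
|---|---|---|---|
| General rule | 0.05 | 2.002 | 0.52 |
| Bonferroni, m = 17 | 0.05/17 = 0.0029 | 3.105 | 0.80 |
| Bonferroni, m = 22 (5 sub-domains assumed) | 0.05/22 = 0.0023 | 3.193 | 0.82 |

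At m = 17, any secondary result with p between 0.0029 and 0.05, that is, observed d between about 0.52 and 0.80, changes status with the sentence applied. For example, an observed d of 0.76 gives t = 2.943 and p = 0.0047, which passes at 0.05 and fails at 0.0029.

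**Step 3: what Holm would change.** Holm orders the p-values and compares them in turn with 0.05/m, 0.05/(m − 1), and so on, stopping at the first failure. Its first threshold is Bonferroni's and the later ones are larger, so it rejects everything that Bonferroni rejects. It controls the same familywise error under the same assumptions. Simulated per-test power, under a normal approximation with m = 22, correlation 0.3 and the primary effect size for every true effect:

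| True effects | Bonferroni | Holm |
|---|---|---|
| 6 of 22 | 45–46% | 47% |
| 16 of 22 | 46% | 51% |
| 22 of 22 | 46% | 57% |

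The gain runs from about 1 point to about 11 points. Only the differences between columns matter here, because the normal approximation puts the power levels somewhat above the noncentral t value (41% at 0.05/22).

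**The case against.** The strongest reply is that this is ordinary drafting: a general default followed by a specific exception. The Bonferroni sentence comes later in the same section and names the secondary outcomes. Saying that the significance value will be corrected presupposes a default to correct. That stands, and it is the more natural reading. It does not fully settle the matter, because the general rule is worded without exception and the word exploratory leaves the scope of the correction open.

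The open divisor is detail that an analysis plan can hold, and it is not a finding here. The cognition count is partly answered as well: section 2.4 says that domains will be analysed and lists six, so the nine subtests describe what is administered.

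Bonferroni is a valid procedure. Holm is an improvement that costs nothing in error control, not the correction of an error.

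Three stronger readings are tempting, and the article does not support them:

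- *That the plan carries a 58% to 74% chance of a false secondary claim.* These figures are 1 − 0.95^17 and 1 − 0.95^26. They require the Bonferroni sentence to be ignored and the tests to be independent, but the HRV measures come from one recording and the BNSS sub-domains from one scale. At m = 22 and correlation 0.5 the figure is 44%, still with no correction applied.
- *That the contradiction costs power, from 82% to 44% at m = 17.* This gives every secondary outcome the effect size stated for the primary analysis only. The loss is also the ordinary price of correcting for multiplicity, not a result of the conflict.
- *That the threshold for every secondary claim is free to be chosen after the results.* That would mean disregarding an explicit correction rule. What is really open is narrower: whether that rule reaches the group-by-time tests.

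**Conclusion.** The concern holds as a minor wording conflict. Section 2.5 states two significance rules that overlap on the secondary outcomes. It does not rank them or say whether the secondary group-by-time tests fall under the corrected one. With 30 per arm and m = 17, a literal reader finds that observed differences of about 0.52 to 0.80 standard deviations are significant under one sentence and not under the other. The count of 17 comes from the article; a larger count, such as the assumed 22, moves the upper end only to 0.82. The primary BNSS analysis keeps its two-sided 5% level and is untouched. The Holm gain rests on assumptions (22 tests, correlation 0.3, primary effect size throughout) and is modest.

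**What to change.** Two changes to section 2.5:

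1. Replace the general statement with: *p < 0.05 (two-sided) for the primary analysis and for the descriptive baseline and dropout comparisons.* Naming those comparisons matters, because otherwise they would be left without a stated level.
2. Replace the Bonferroni sentence with: *The group-by-time tests of all listed secondary outcomes form one family, controlled at 0.05 by Holm's procedure. The members of the family (outcomes and visits, with cognition represented by the six listed MATRICS domains) are fixed before unblinding.*

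The sponsor should decide, and state, whether the associations between sleep and negative symptoms belong to the family, since the article lists them among the secondary outcomes. If the sponsor prefers to keep Bonferroni, the two rules still need to be reconciled.

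**Cost.** Wording only; no patients and no data. Secondary results between the Holm threshold and 0.05 can no longer be called significant by appeal to the general sentence. They already fail under the Bonferroni sentence, apart from any that Holm admits.

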## 2. Materials and Methods

Design: We proposed a randomized, double-blind, sham-controlled clinical trial to test the effects of the accelerated iTBS protocol in participants with schizophrenia with negative symptoms (CONSORT—Figure 1). The study is conducted in accordance with the Declaration of Helsinki and has been approved by the Research Ethics Committee of the Federal University of São Paulo (UNIFESP) as of 14 September 2023 and registered in The Brazilian Registry of Clinical Trials (ReBEC) (CAEE: 71102823.4.0000.5505).

*Participants*:

We will recruit 60 volunteers, aged between 18 and 50 years of both genders, who have been diagnosed with schizophrenia according to the criteria of the Diagnostic and Statistical Manual of Mental Disorders (DSM-5), through an evaluation conducted via the Structured Clinical Interview for DSM-5 (SCID-5) and who present negative symptoms of moderate intensity (score ≥ 20 on the BNSS). Participants must have stable medication use, with no changes in antipsychotics in the three months prior to inclusion, and must not be using medications that could lower the seizure threshold, except for antipsychotics. Additionally, participants should not have a history of substance dependence or alcohol use in the past four weeks. In the case of smokers, the number of cigarettes and the last use will be documented. Regarding neuromodulation, participants should not have undergone any brain stimulation protocols in the past year prior to study enrollment. All participants must sign the informed consent form to participate in the study.

Participants will be allocated into two groups (intervention and sham), with 30 subjects per group. The statistical power for the primary analysis with this sample size is estimated to be β = 0.82. This calculation assumes (1) the use of mixed linear regression models for hypothesis testing, which will assess the interaction between time (baseline vs. T1) and treatment (intervention vs. sham), (2) a moderate effect size (f = 0.38), and (3) a significance level of 5% (two-tailed).

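### The plan tests a group-by-time interaction but words the reported effect as a post-intervention difference; a model with a common baseline mean would make the two agree and use baseline BNSS more efficiently.

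*Protocol article*

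**What the plan says.** Section 2.5 of the protocol article defines the tested effect: "The treatment effect will be estimated through the interaction between the intervention group (intervention or sham) and the assessment time (T0, T1, and T2"). T0 is therefore one of the outcome times. The next sentence describes the reporting: "Effect estimates will be presented as post-intervention mean differences, along with 95% confidence intervals", together with p-values and Cohen's d. The covariates named are the Calgary depression score, CGI-S and GAD-7. The section gives no model formula. It does not say whether the arms may have different fitted means at T0 or are constrained to share one.

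The sample-size paragraph in section 2 refers to the "interaction between time (baseline vs. T1) and treatment (intervention vs. sham"). It gives 30 participants per arm, "a moderate effect size (f = 0.38"), "a significance level of 5% (two-tailed") and a power of 0.82.

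**The concern.** In the standard group-by-time model, with terms for group, time and their product, two quantities at T1 are easily confused:

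- The **interaction** is the difference between arms in change from T0 to T1.
- The **post-intervention difference** is the difference between arms at T1 itself. It equals the group term plus the interaction, so it carries any chance imbalance in BNSS at T0.

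Their point estimates and standard errors differ. If the p-value comes from the first and the estimate with its interval from the second, the published interval could contradict the published test. The trial would also have two candidate primary results.

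A second issue does not depend on how the reporting sentence is read. In a randomised trial the true T0 means of the arms are equal. A difference-in-change contrast does not use this, and so is less precise than it could be in a trial of 60 patients.

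**Working it through.** **Inputs from the article:** n = 30 per arm; f = 0.38, so d = 2f = 0.76 for two equal groups; two-sided α = 0.05; stated power 0.82. 
**Assumptions, not in the article:** the T0–T1 correlation ρ of BNSS (range 0.3 to 0.9), equal variance σ² at T0 and T1 unless stated otherwise, and no dropout. The article does not say whether d is in SDs of change or of the raw T1 score, so both are shown.

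**Step 1. The plan's own figure.** Noncentral F with 1 and 58 df and λ = f²N = 0.38² × 60 = 8.664 gives power 0.825. The stated 0.82 is reproduced, as a plain two-group comparison with d = 0.76.

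**Step 2. Variance of each T1 contrast**, in units of 2σ²/n:

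- interaction (difference in change): 2(1−ρ)
- post-intervention difference: 1
- group×T1 coefficient in the common-T0-mean model: 1−ρ²

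| ρ | Interaction | Post-intervention difference | Common T0 mean |
|---|---|---|---|
| 0.3 | 1.40 | 1.00 | 0.91 |
| 0.5 | 1.00 | 1.00 | 0.75 |
| 0.7 | 0.60 | 1.00 | 0.51 |

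Generalised least squares on a three-time-point model with compound symmetry gave the same values. The common-mean variance relative to the interaction is (1−ρ²)/[2(1−ρ)] = (1+ρ)/2, that is 0.65, 0.75, 0.85 and 0.95 at ρ = 0.3, 0.5, 0.7 and 0.9. At ρ = 0.5 this corresponds to 60 × 0.75 = 45 patients for the same precision.

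**Step 3. Power, d = 0.76 in SDs of change.** Interaction: λ = 15 × 0.76² = 8.664. Common mean: λ = 8.664/[(1+ρ)/2], with 57 df.

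| ρ | Interaction | Common T0 mean |
|---|---|---|
| 0.3 | 0.825 | 0.948 |
| 0.5 | 0.825 | 0.916 |
| 0.7 | 0.825 | 0.881 |
| 0.9 | 0.825 | 0.843 |

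**Step 4. Power, d = 0.76 in SDs of the raw T1 score.** Interaction: λ = 8.664/[2(1−ρ)]. Common mean: λ = 8.664/(1−ρ²).

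| ρ | Interaction | Common T0 mean |
|---|---|---|
| 0.3 | 0.687 | 0.858 |
| 0.5 | 0.825 | 0.916 |
| 0.7 | 0.962 | 0.982 |

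**Step 5. Effect of the entry rule.** BNSS ≥ 20 at entry may narrow the T0 variance. Suppose it halves it (an assumption), with ρ now the correlation before selection and the regression of T1 on T0 unchanged. The change variance becomes (1−ρ²) + 0.5(1−ρ)² and the adjusted variance stays 1−ρ². The ratio is (1+ρ)/[(1+ρ) + 0.5(1−ρ)]: 1.3/1.65 = 0.79, 1.5/1.75 = 0.86 and 1.7/1.85 = 0.92 at ρ = 0.3, 0.5 and 0.7. With d in SDs of change, power is then about 0.90, 0.88 and 0.86, against 0.825 for the interaction.

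**Step 6. How often the two planned quantities could conflict.** In 40,000 simulated trials with 30 per arm and d = 0.76 in raw T1 SDs, the interaction test and the post-intervention test disagreed on significance in about 20% of trials at ρ = 0.5 and 18% at ρ = 0.7. With no effect they disagreed in 8 to 9%. Each test rejected in about 5% of null trials, so each is valid on its own.

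**The case against.** The strongest reply is that there is no contradiction. One sentence says how the effect is estimated and the next how it is presented, so the reported difference may simply be the interaction contrast after treatment. The sample-size paragraph also powers the interaction, and nowhere does the article say that a separate unadjusted T1 comparison will be run. This stands: the mismatch follows from the wording as it is, but is not certain. It does not remove the efficiency point.

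Second, the free group effect at T0 is inferred from common practice. Without a formula, a model that already has a common T0 mean would also fit the text, and an article may leave such detail to a fuller document. This stands too, and is why the request is to state the model.

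Third, the gain may be small. Stable patients reassessed soon after treatment could correlate above 0.7, and at ρ = 0.9 power moves only from 0.825 to 0.843. This stands as a limit on size, not on direction. For any variances, the change-score variance exceeds the adjusted variance by (σ0 − ρσ1)², which is never negative.

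Two stronger readings are tempting and not supported. A reader might infer that the planned test is biased or inflates type I error; it does neither. A reader might also infer that baseline BNSS was wrongly left off the covariate list. T0 BNSS is already in the model as an outcome, so it should not be a covariate there as well.

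**Conclusion.** The point holds as a matter of clarity and efficiency, not validity. As worded, section 2.5 allows an estimate and interval for one quantity beside a p-value for another; whether that is intended cannot be settled from the article. On either reading, the usual interaction contrast uses baseline BNSS less well than randomisation permits.

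The size is uncertain because the article gives neither ρ nor the SD scale of f = 0.38. Over ρ = 0.3 to 0.7 with equal variances, the gain in power over the interaction is about 12 to 6 percentage points if d is in SDs of change, and about 17 to 2 points if d is in raw-score SDs. It is smaller if the entry threshold compresses T0 variance. These figures assume complete data and a free T0 group effect in the planned model.

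The common-mean constraint requires that allocation does not affect T0 scores. Section 2 mentions randomisation before the baseline clinical evaluation, but assessors and participants are blinded and treatment has not begun, so the constraint is reasonable.

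**What to change.** Before unblinding, specify the primary mixed model with T0, T1 and T2 as outcomes, a common T0 mean for both arms, and terms for time, group×T1 and group×T2, with no group effect at T0. Keep every participant with any BNSS data, in line with the intention-to-treat and restricted maximum likelihood statements in section 2.5. Name the group×T1 coefficient as the adjusted mean difference, and take the estimate, 95% CI, p-value and Cohen's d all from it. Use the same form for each repeatedly measured secondary outcome.

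A model with only T1 and T2 as outcomes and baseline BNSS as covariate is not an exact substitute: it drops participants who have T0 data only, which conflicts with the plan to use all data.

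The cost is one line of model specification and a reworded reporting sentence. No new data, patients or visits are needed. If the sponsor prefers the unconstrained interaction, the reporting sentence should at least say that the estimate and interval are those of the interaction contrast.

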A recent meta-analysis that included 12 intervention studies using intermittent theta burst stimulation (iTBS) for negative symptoms showed that a higher total number of pulses, compared to relatively lower numbers of pulses, presents a greater effect size, suggesting that the efficacy of iTBS treatment is dose-dependent [11]. Definitions of parameters such as intensity, frequency, duration, waveform, and stimulation site need to be better defined. In this regard, accelerated TMS (aTMS) protocols, characterized by two or more sessions of TMS in a single day, have emerged as an effective alternative and appear to be a viable strategy for reducing total treatment time; it enables a greater number of sessions per day and delivers the same number of pulses and sessions of a conventional 6-week treatment within a single week, sometimes with efficacy surpassing that of daily session doses [12,13,14]. Despite its potential, the literature about the use of intermittent theta burst stimulation (iTBS) for treating negative symptoms of schizophrenia is still limited, especially regarding the type of protocol and the brain area to be stimulated, although the left dorsolateral prefrontal cortex (DLPFC) has shown promising results [15,16,17,18,19].

The studies conducted to date have limitations that hinder a better understanding of the true potential of intermittent theta burst stimulation (iTBS) for negative symptoms in schizophrenia, including the following: 1—few double-blind, randomized clinical trials; 2—small sample sizes; 3—the use of instruments that do not allow for the assessment of sub-domains of negative symptoms; 4—a lack of control for potential confounders in the evaluation of negative symptoms, such as depressive and extrapyramidal symptoms [15,16,17,20,21].

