In this context, a clinical trial using an accelerated iTBS protocol in the left dorsolateral prefrontal cortex (DLPFC) is necessary, considering the positive results from studies conducted with conventional high-frequency rTMS protocols and the fact that accelerated protocols using iTBS have been demonstrated to be more effective [35]. The primary objective of the study will be to evaluate the efficacy of an accelerated transcranial magnetic stimulation (theta-burst—iTBS) protocol on reducing negative symptoms in patients with schizophrenia through a double-blind, randomized, sham-controlled clinical trial. The protocol aims to provide a greater number of sessions in a short period of time while maintaining the feasibility of application. The study will include multimodal assessments, including clinical, neuropsychological, sleep, and HRV evaluations, in order to establish the mechanisms of stabilization of these symptoms. We hypothesize a 20% reduction in BNSS scores in the active group, as well as improvements in disorder-related aspects, including sleep patterns, symptom severity, and cognition.

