### 2.2. Clinical Assessment

Clinical assessment will be applied three times: at baseline (T0), after the iTBS (T1), and at a 30-day follow-up (T2). The validated Portuguese versions for the Brazilian population of the Brief Negative Symptom Scale (BNSS) [39], and the Positive and Negative Syndrome Scale (PANSS) [40] will be applied to assess negative symptoms and clinical symptomatology. Additionally, the translated and validated versions of the Pittsburgh Sleep Quality Index (PSQI) [41] and the Epworth Sleepiness Scale (ESE) [42] will be used to assess sleep. Generalized Anxiety Disorder-7 (GAD-7) [43] and Clinical Global Impression (CGI) [44], validated instruments for evaluating symptom severity in patients with schizophrenia in Brazil, will also be employed. The Calgary Depression Severity Scale (CDSS) [45] will be applied to check for depressive symptoms. Finally, the Simpson–Angus Scale (SAS) [46] will be administered to identify medication-induced parkinsonian symptoms. All tests will be conducted by trained psychiatrists.

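### The covariates CDSS, CGI-S and GAD-7 are not tied to baseline, and if visit-level values enter the models the primary iTBS effect could be attenuated

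*Protocol article*

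**What the plan says.** Section 2.5 (Statistical Analysis) analyses each measure with a mixed-effects linear model over T0, T1 and T2, takes the group-by-time interaction as the treatment effect, and commits to intention to treat. It then names three covariates:

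- "The following covariates will be included in the models: the Calgary Depression Severity Scale score". The reasons given are that depression can confound the rating of negative symptoms and that severely depressed people are not enrolled.
- "the total score of the Clinical Global Impression-Severity scale (CGI-S), since the severity of illness may influence treatment response".
- "the Generalized Anxiety Disorder 7-item scale (GAD-7), due to anxiety symptoms".

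None of the three carries a time point.

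Section 2.2 (Clinical Assessment) sets the schedule: "Clinical assessment will be applied three times: at baseline (T0), after the iTBS (T1), and at a 30-day follow-up (T2"). All three scales belong to that assessment: "The Calgary Depression Severity Scale (CDSS) [45] will be applied to check for depressive symptoms", and "Generalized Anxiety Disorder-7 (GAD-7) [43] and Clinical Global Impression (CGI) [44], validated instruments for evaluating symptom severity" are used as well.

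The hypothesis in section 1 (Introduction) expects iTBS to bring "improvements in disorder-related aspects, including sleep patterns, symptom severity, and cognition".

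**The concern.** A covariate measured before randomisation cannot be changed by treatment, so adjusting for it leaves the randomised comparison intact. A covariate measured at T1 or T2 can be changed by treatment. Holding it fixed then asks a different question: how far BNSS differs between arms among patients with the same depression, anxiety and global severity at that visit.

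CGI-S is the serious case. It rates overall illness severity, and the patients are selected for negative symptoms, so it overlaps with the BNSS. By the trial's own hypothesis, symptom severity should improve under iTBS. Adjusting for CGI-S at T1 would remove part of the effect under test. The expectation that treatment moves CDSS or GAD-7 is weaker, because the hypothesis names neither depression nor anxiety.

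What is at stake is the primary estimate. As worded, two analysts could follow the article faithfully and estimate two different quantities, and the choice could be made after the data are seen.

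**Working it through.** **1. What the stated reasons imply about timing**

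| Covariate | Reason in section 2.5 | Timing it suggests |
|---|---|---|
| CDSS | confounds the rating of negative symptoms | same visit as the rating |
| CDSS | severe depression is excluded | baseline (a fact about enrolment) |
| CGI-S | severity may affect response | baseline (precedes response) |
| GAD-7 | anxiety symptoms | neither |

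The Introduction, which faults earlier trials for not controlling "potential confounders in the evaluation of negative symptoms, such as depressive and extrapyramidal symptoms", also speaks of the rating itself and so leans to same-visit values. The text does not settle the matter.

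**2. The plan's own power figure**

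Inputs from section 2: 30 per group, f = 0.38, two-sided 5%, stated power 0.82. For two groups d = 2f = 0.76.

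- Noncentral F with 1 and 58 degrees of freedom, λ = f² × 60 = 0.1444 × 60 = 8.66: power 0.825.
- Normal approximation: 0.76 / √(2/30) = 0.76 / 0.2582 = 2.943; Φ(2.943 − 1.96) = 0.837.

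The stated 0.82 reproduces as a two-group comparison without covariates. It serves here as the reference.

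**3. Effect of a visit-level covariate**

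Let r be the within-arm correlation of BNSS change with CGI-S change, and d_c the iTBS effect on CGI-S in SD units. **Neither is in the article; both are assumed.** For one covariate:

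- adjusted effect = 0.76 − r × d_c
- standard error = √(1 − r²) × √(2/30) × √(1 + d_c²/4)
- power = Φ(adjusted effect / SE − 1.96)

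The first factor of the SE credits the smaller residual SD. The last charges for the correlation between covariate and group.

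Example, r = 0.5 and d_c = 0.5: effect 0.76 − 0.25 = 0.51; SE = 0.866 × 0.2582 × 1.031 = 0.2305; 0.51 / 0.2305 = 2.213; power Φ(0.253) = 0.60.

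| r | d_c | Adjusted effect | Share kept | Power |
|---|---|---|---|---|
| 0.3 to 0.7 | 0 | 0.76 | 100% | 0.87 to 0.99 |
| 0.3 | 0.2 | 0.70 | 92% | 0.81 |
| 0.5 | 0.2 | 0.66 | 87% | 0.84 |
| 0.7 | 0.2 | 0.62 | 82% | 0.92 |
| 0.5 | 0.4 | 0.56 | 74% | 0.69 |
| 0.5 | 0.5 | 0.51 | 67% | 0.60 |
| 0.5 | 0.76 | 0.38 | 50% | 0.36 |
| 0.7 | 0.6 | 0.34 | 45% | 0.42 |
| 0.7 | 0.76 | 0.23 | 30% | 0.21 |

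When d_c is small, the gain in precision can offset the attenuation and power need not fall. The estimate is still too small whenever d_c is above zero.

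**4. Check by simulation**

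A REML random-intercept model was fitted with 30 per arm, three visits, a true effect of 0.76 and 100 runs per setting.

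| r | d_c | Visit-level covariate: estimate (power) | T0 covariate only: estimate (power) |
|---|---|---|---|
| 0.5 | 0 | 0.78 (0.97) | 0.78 (0.90) |
| 0.5 | 0.4 | 0.57 (0.72) | 0.78 (0.89) |
| 0.5 | 0.76 | 0.38 (0.36) | 0.77 (0.81) |
| 0.7 | 0.76 | 0.23 (0.19) | 0.73 (0.84) |

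The visit-level estimates follow the formula. With the T0 value only, the estimate stays near 0.76 apart from simulation error.

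**The case against.** The strongest reply is that the article never says post-treatment values will be used. The reason for CGI-S, the scale on which the numerical argument rests, describes something that precedes response, and the remark on excluding severe depression is about enrolment. Covariate timing is also a detail that an analysis plan commonly settles.

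Most of this stands, and it limits the claim. A reader might infer that the plan will adjust away the iTBS effect. The text does not support that: it leaves the timing open, so the bias is conditional. A reader might also take a large loss of power as the expected result. That follows only from unfavourable assumed inputs; with an assumed CGI-S effect of 0.2 SD power stays at about 0.8 or above, and with none there is no bias.

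The reply does not remove the point. The article names the covariates and justifies each one, and its reason for CDSS favours same-visit scores. Following the text as written can therefore lead to a model that no longer estimates the intention-to-treat effect promised in the same section.

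A reader might add that the Simpson–Angus Scale is missing from the covariates, since the Introduction criticises uncontrolled extrapyramidal symptoms. Omitting a baseline covariate does not bias a randomised comparison, so adding it is optional and not part of this correction.

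**Conclusion.** The point holds in conditional form: covariate timing in the primary model is ambiguous, and one of the two readings can bias the group-by-time coefficient toward no effect. This requires both that visit-level values enter and that iTBS changes them. CGI-S carries the main risk.

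The size cannot be derived from the article. Over the assumed range, a true 0.76 SD is estimated as 0.76 if CGI-S is unmoved, 0.70 under mild inputs, 0.51 in the middle (power about 0.6) and 0.23 at the far end (power about 0.2). These figures treat one covariate at a time. No size is offered for CDSS or GAD-7.

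**What to change.** Add to section 2.5, in substance: only the T0 values of CDSS, CGI-S and GAD-7 enter the primary and other efficacy models, and no value measured after randomisation is used as a covariate in them. If the aim is to learn whether a change in negative symptoms is independent of depression or anxiety, report adjustment for post-randomisation values as a separate analysis, labelled sensitivity or mediation.

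The cost is one sentence. All T0 values are already collected, and the sample size and visit schedule do not change. A T0 covariate entered only as a main effect leaves the group-by-time estimate essentially unchanged when data are complete, so little is gained or lost in precision.
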